### Statistical methods

Sample size calculation is based on detecting a difference of 0.6 points in DAS28 change from baseline between the two groups; 0.6 was chosen because it is the minimum therapeutic response according to EULAR [38]. Assuming a standard deviation of 0.6 [28] and using a two-sided test at the 5% significance level, enrolling 16 participants per group would yield 80% power (epiR package 0.9-30). Anticipating a 25% dropout rate, the target sample size was thus set at 40 participants.

After data cleaning, preliminary analyses will investigate the pattern of missing baseline and follow-up data. Baseline characteristics per group will be presented as mean, median, and standard deviations for quantitative variables, and as absolute and relative frequency for qualitative variables. Descriptive statistics will be provided for the intention-to-treat population to explore whether the randomization results in a balanced distribution of participants’ characteristics between the two groups.

All baseline analyses will be performed in accordance with intention-to-treat principles, regardless of the subject's presence at intermediate visits, the degree of compliance with the periodontal treatment, or any change in RA medication.

The main analysis will be a comparison between the two study groups concerning the change in the DAS28 scores from baseline to 3 months in a multivariate model, adjusted for clinical center, and considering the rest of the independent measures (including any change in RA medication) as possible modifying factors. The data will be secondarily analyzed using the ‘per protocol’ approach, in which the analysis will be restricted to participants who have complied with the treatment protocol (SRP, ATB, and OHI) and have had no changes in RA medication during study participation.

In addition to the primary analysis, five binary outcomes for DAS28 at 3 months (a relative decrease greater than 10%, a 3-month level of less than 3.2, an absolute decrease greater than 0.6, a relative increase greater than 10% and an absolute increase greater than 0.6) will be evaluated in logistic regression models. For secondary outcomes, continuous variables will be analyzed through analysis of covariance, using a model similar to that specified for the primary outcome.

Missing outcome data will be handled as described by Ware *et al.*[40] and Little *et al.*[41]. For participants who discontinue any of the periodontal treatments (SRP, ATB, or OHI) because of AEs or simple inconvenience, efforts will be made to obtain their consent for the collection of data on outcomes. Second, we will limit the burden and inconvenience of data collection on the participants, and make the study experience as positive as possible. For example, the DAS28 assessment will be performed in the clinical center where participants are usually followed for their RA treatment. Third, investigators will be trained that keeping participants in the trial until the end is important, regardless of whether they continue to receive the assigned treatment. This information will also be conveyed to study participants. Finally, missing outcome data will be handled using estimating-equation methods [42,43]. Complete cases will be weighted by the inverse of an estimate of the probability being observed. Efficacy of periodontal treatment will be assessed, as will the correlation between clinical response to periodontal treatment and DAS28 scores. The proportion of subjects who have one or more AEs in the two groups will be compared by Fisher's exact test. Analyses will be performed by R software (http://www.R-project.org).

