### General design

The ESPERA (Experimental Study of PEriodontitis and Rheumatoid Arthritis) trial is an open-labeled, randomized controlled clinical study. This trial is bicentric (Toulouse and Bordeaux University hospitals, France), with two parallel groups (‘immediate’ periodontal treatment versus ‘delayed’ periodontal treatment, with a balanced 1:1 treatment allocation), and with 3 months follow-up for both groups.

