## Discussion

Evidence-based management of potential aggravating factors in subjects with active RA could be of clinical importance. We hypothesize that periodontitis could be an aggravating factor for RA. However, there are few randomized controlled trials about the effects of periodontal treatment on the clinical parameters of RA. The ESPERA trial is designed to determine if non-surgical periodontal treatment could improve clinical outcomes in patients with active RA, and also improve their QOL.

Our trial has a small sample size, and a potential lack of power. However, the ESPERA trial has a conventional 80% power to detect a difference of 0.6 points in DAS28 change from baseline between the two groups, and 0.6 is the minimum therapeutic response according to EULAR [38]. We acknowledge that 0.6 mean improvement could be considered as relatively large, but two other trials have shown such an improvement [27,28]. Furthermore, the sample size corresponds to our source population of outpatients with both RA and periodontitis, as reported in a recently published observational study [45]. Because small trial size should not be used to justify low-quality trials, efforts will be made to minimize sources of bias, and to enhance the reliability of the results of the ESPERA trial. Selection bias will be prevented through randomization, and special attention will be paid to securing strict implementation of the random sequence. Performance bias will be unavoidable, because there is no possible placebo for periodontal treatment; however, detection bias will be prevented through the blinding of RA outcome assessors. Finally, attrition bias will be assessed at the end of the trial.

A strong feature of the current trial is that the expected benefit for the patient could be a contribution to the stabilization of the disease, or a slight clinical improvement in RA. This could reduce the need for escalating therapy related to insufficient control of the disease, and improve QOL in patients with RA. In long term, periodontal treatment could be integrated in the rheumatologist’s associated therapeutic arsenal.

Results of this trial could have an influence on clinical practice, and potentially contribute to further development of new research directions for both odontologists and rheumatologists.

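### The target of 40 covers 20% dropout, not the 25% stated; at 25%, 30 evaluable participants remain and power is about 78%

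*Protocol article*

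**What the plan says.** All planning inputs are in the protocol article under Statistical methods. The target effect is given as "Sample size calculation is based on detecting a difference of 0.6 points in DAS28 change from baseline between the two groups". The standard deviation is 0.6, taken from one cited study. The test is described as "using a two-sided test at the 5% significance level". From these the article concludes that "enrolling 16 participants per group would yield 80% power", and it goes on: "Anticipating a 25% dropout rate, the target sample size was thus set at 40 participants".

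The General design section specifies two parallel groups "with a balanced 1:1 treatment allocation". The Abstract (Methods/design) confirms that 40 is the number to be randomized, so the 40 is not a misprint in one place.

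The Discussion first admits that the trial is small and may lack power, and then answers that "the ESPERA trial has a conventional 80% power to detect a difference of 0.6 points in DAS28 change from baseline". No dropout rate is attached to that statement. Nothing elsewhere in the article gives another derivation of 40 or a dropout rate other than 25%.

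**The concern.** The article presents 40 as the result of allowing for 25% dropout from a requirement of 32. To end with 32 evaluable participants after a proportion d is lost, the requirement must be divided by (1 − d). Multiplying it by (1 + d) gives too small a number, because the loss applies to the enlarged sample and not to the 32. The stated 40 matches the multiplication exactly.

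What is at stake is the accuracy of the power statement. The Discussion uses 80% power to defend the trial's size. If dropout is as anticipated, the article's own inputs give slightly less than that, and a null result would be read against a type II error a little lower than the design provides.

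**Working it through.** **Inputs** (all from Statistical methods, except the allocation, which is in General design): difference δ = 0.6; SD σ = 0.6; two-sided α = 0.05, so z = 1.95996; power 80%, so z = 0.84162; 1:1 allocation; dropout d = 0.25; target N = 40.

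**Step 1. Reproduce the 16 per group.**
n per group = 2 (1.95996 + 0.84162)² (σ/δ)² = 2 × 2.80158² × 1 = 15.70, rounded up to 16. Power at 16 per group = Φ(√(16/2) × δ/σ − 1.95996) = Φ(2.828 − 1.960) = 80.7%. The stated figure is reproduced by the normal approximation with a two-sided test (one-sided would need 13).

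**Step 2. Reproduce the 40.**

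| Rule | Calculation | Total |
|---|---|---|
| Multiply by (1 + d) | 32 × 1.25 | 40 |
| Divide by (1 − d) | 32 / 0.75 = 42.7 | 43 |
| Divide by (1 − d), per arm | 16 / 0.75 = 21.3, so 22 per arm | 44 |

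Only the first rule gives 40. The dropout that 40 can absorb while keeping 32 is 1 − 32/40 = 20%.

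**Step 3. What 40 delivers at 25% dropout.**
40 × 0.75 = 30, or 15 per group if losses are equal.

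**Step 4. Power at 15 per group, same formula.**
Φ(√(15/2) × 1 − 1.95996) = Φ(2.739 − 1.960) = 78.2%. Type II error is 21.8%. If the 25% loss falls at random within each arm of 20, so that arm sizes vary, average power is about 77.6%.

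**Step 5. Detectable difference at 15 per group with 80% power.**
0.6 × √(2/15) × 2.80158 = 0.614, against 0.60 planned.

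**Step 6. Sensitivity to the reference distribution.** This assumes a two-sample t test, which the article does not name.

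| Evaluable per group | Normal approximation | Noncentral t |
|---|---|---|
| 15 | 78.2% | 75.3% |
| 16 | 80.7% | 78.1% |
| 17 | 83.0% | 80.7% |

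At 15 per group, 78.2 − 75.3 = 2.9 points come from the change of reference distribution. The dropout slip itself, from 16 to 15 per group, costs 80.7 − 78.2 = 2.5 points.

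**The case against.** Several arguments bear on the size of the effect; none repairs the arithmetic.

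- **The loss is small.** This stands. By the article's own formula, power at 25% dropout is 1.8 points under 80%. Starting from the unrounded 15.70 per group, 31.4 / 0.75 = 41.9, or 42 participants, only two above the target. But the article fixes 16 per group, and even 42 exceeds 40.
- **Dropout is not the same as a missing primary outcome.** Under Outcomes, DAS28 data from interim or later visits replace an absent V4 assessment, and the Statistical methods section plans to keep collecting outcomes from those who stop treatment. Thirty evaluable is therefore the pessimistic end. This stands as a limit on the consequence, but the stated calculation still has to agree with its own 25%.
- **The planned model is adjusted.** At 15 per group, covariates explaining about 1 − 15/15.70 = 4% of outcome variance would restore 80% by the normal formula. The article gives no such figure and takes no credit for one, so this remains an assumption.
- **Missing outcomes are handled by inverse-probability weighting.** That addresses bias and does not replace lost participants.
- **The Discussion already warns of low power.** It does, and it ties the sample size to the available source population. The 80% figure is nevertheless offered as the reply to that warning.

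A reader might go further and infer that 16 per group is itself wrong, or that the type II error is about 25% and the detectable difference 0.64. The document does not support this. The 16 is reproduced by a standard planning formula, and the less favourable figures depend on a two-sample t test. The article instead plans a centre-adjusted multivariate model, with weighted estimating equations for missing outcomes.

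**Conclusion.** The dropout allowance is wrong as written: 40 comes from multiplying by 1.25 and covers 20% dropout. At the stated 25%, 30 evaluable participants remain, two below the 32 that the article links to 80% power, and the target is 3 to 4 participants short of its own rule.

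Power is then about 78%, and the difference detectable with 80% power is about 0.61. These figures assume the article's δ and SD, equal losses in the two arms, an unadjusted comparison under the normal approximation, and no DAS28 value recovered for those who drop out. A t reference would put power at about 75%; that is a side note about small samples, not a second error in the plan.

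Severity is minor. A reader might conclude that the trial is materially underpowered or must enrol more participants. The shortfall of about 2 points does not support that, and the estimand, analysis and conduct are unaffected.

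**What to change.** Restate the figures in two places, Statistical methods and Discussion, using one of these options:

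1. State that 40 participants allow for 20% dropout, leaving 32 evaluable and 80% power by the normal approximation.
2. Keep the 25% dropout and state that 30 evaluable participants give about 78% power by the normal approximation (about 75% if a t reference is assumed).

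In the Discussion, attach the chosen dropout rate and power to the 80% claim so that the two sections agree. If the sponsor wishes to cite a gain from covariate adjustment, it should appear as a separate figure with its assumed explained variance.

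The cost is wording only. The target of 40 can stay. Under option 1 the planned dropout becomes less cautious; under option 2 the stated power is slightly lower.

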### Outcomes

The primary outcome is change in the DAS28 between V1 and V4. Secondary outcomes are difference in matching ACR20, ACR50, and ACR70 criteria, and changes in HAQ and GOHAI scores, between V1 and V4.

The assigned rheumatologist, who will be blinded to the patient’s assigned periodontal treatment group, will assess DAS28 [38], which is a continuous composite score (0 to 9.71) by considering the number of tender and swollen joints (out of the 28 evaluated joints); the ESR, which measures the degree of inflammation in the blood; and the patient’s global assessment of health. They will also assess the improvement in RA using the ACR criteria [32], and will review medical forms for each participant’s safety. The same rheumatologist will perform outcomes measures between V1 and V4. The health status of the enrolled subjects will also be assessed by the same rheumatologist throughout the monthly routine visits during the 3 months follow-up period. Interim or post-V4 data will be used in case of absence at V4.

Assessed dental investigators will be responsible for performing a standardized periodontal probing assessment at V1 and V4. The full-mouth periodontal probing will be performed using a constant pressure probe (Florida Probe^®^; Gainesville, Fl, USA), from six sites per tooth (mesiobuccal, mid-buccal, distobuccal, mesiolingual, mid-lingual and distolingual). Periodontal assessment will include measurement of periodontal pocket depth (PPD) in millimeters, clinical attachment level (CAL; in millimeters) and bleeding on probing (yes/no). No radiographs will be taken. Periodontitis will be defined by the presence of at least one site with PPD ≥ 4 mm and CAL ≥ 3 mm on at least 4 different teeth.

Finally, participants will self-complete questionnaires assessing QOL (HAQ and GOHAI). They will also be asked to complete initial and final questionnaires at V1 and V4, which will assess medical, social, and oral health behavior information, and assess changes during the 3-month follow-up period. Adverse events (AEs) during the follow-up period will be reported, and these will include unexpected study-related events and serious AEs regardless of cause.

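### The primary DAS28 change model commits only to center as a covariate; baseline (V1) DAS28 is not prespecified, which forgoes a modest, free gain in precision

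*Protocol article*

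**What the plan says.** Under Outcomes, the Protocol article defines the endpoint: "The primary outcome is change in the DAS28 between V1 and V4". Under Statistical methods, the main analysis is a between-group comparison of "the change in the DAS28 scores from baseline to 3 months in a multivariate model, adjusted for clinical center", continuing with "considering the rest of the independent measures (including any change in RA medication) as possible modifying factors". Center is therefore the only covariate that is certain to be in the model. The only other variable named, a change in RA medication, arises after randomization. V1 DAS28 is not named.

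For the secondary outcomes, "continuous variables will be analyzed through analysis of covariance, using a model similar to that specified for the primary outcome". This covers HAQ and GOHAI, and no covariate is named there either.

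Two other places bear on the point. Randomization is stratified by center and not by DAS28. Baseline balance between the groups is to be described, with no stated consequence for the model.

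**The concern.** A change score treats each point of baseline DAS28 as if it carried over fully to three months, that is, as if the slope of V4 on V1 were 1. Patients enter this trial because a variable score lies between 3.2 and 5.1 (V1 inclusion criteria), so some regression to the mean, and hence a slope below 1, is to be expected.

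A slope below 1 has two consequences. First, the change score contains variance that V1 DAS28 could explain, and the test is less precise than it could be. Second, a chance difference in mean V1 DAS28 between the arms is only partly removed, and the remainder goes into the treatment estimate. In a trial of 40 patients such differences need not be small.

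The open wording also leaves it undecided whether V1 DAS28 enters the primary model. That choice is better made before outcome data are seen.

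**Working it through.** **Inputs from the Protocol article (Statistical methods unless noted)**
- Target: "detecting a difference of 0.6 points in DAS28 change from baseline between the two groups".
- Variability: "Assuming a standard deviation of 0.6", which the document applies to the change score.
- Test: "using a two-sided test at the 5% significance level".
- Size: "enrolling 16 participants per group would yield 80% power"; 40 enrolled in total with 25% dropout anticipated.
- Entry range of DAS28 at V1: 3.2 to 5.1, a width of 1.9 (V1 inclusion criteria).

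**Inputs assumed, because the document does not give them**
- Baseline SD s₀ of 0.40 to 0.55. The upper value is that of a uniform spread over the entry range: 1.9/√12 = 0.548.
- Slope b of V4 on V1 DAS28 of 0.5 to 0.8, with b = 1 as the limiting case.

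**Step 1. The plan's own figure.** n per arm = 2(1.960 + 0.842)² × 0.6²/0.6² = 15.7, rounded up to 16. Power at 16 per arm is 80.7% by the normal approximation and 78.1% by the noncentral t. The stated 16 per group reproduces. It rests on the unadjusted change score.

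**Step 2. Reference power without baseline adjustment.** With 25% loss, 40 × 0.75 = 30 patients remain, or 15 per arm. With difference 0.6 and SD 0.6, the noncentral t gives 75%.

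**Step 3. Residual variance with V1 DAS28 in the model.** The slope of change on V1 DAS28 is b − 1, so

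residual variance = 0.36 − (1 − b)² s₀².

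At s₀ = 0.55 and b = 0.5 this is 0.36 − 0.25 × 0.3025 = 0.284, a residual SD of 0.533. At s₀ = 0.40 and b = 0.8 it is 0.36 − 0.04 × 0.16 = 0.354, a residual SD of 0.595.

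**Step 4. Power at 15 per arm (noncentral t), difference 0.6**

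| Baseline SD | Slope | Residual SD | Variance saved | Power |
|---|---|---|---|---|
| 0.40 | 0.5 | 0.566 | 11% | 80% |
| 0.40 | 0.8 | 0.595 | 2% | 76% |
| 0.55 | 0.5 | 0.533 | 21% | 84% |
| 0.55 | 0.8 | 0.590 | 3% | 77% |
| any | 1.0 | 0.600 | 0% | 75% |

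Charging degrees of freedom for center and baseline changes these figures by about 0.2 points.

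**Step 5. Chance imbalance at 15 per arm.** The SD of the difference in mean V1 DAS28 is s₀√(2/15), which is 0.146 at s₀ = 0.40 and 0.201 at s₀ = 0.55. The shift in the unadjusted estimate for a one-SD imbalance is (1 − b) times this:
- smallest case: 0.2 × 0.146 = 0.03 points;
- largest case: 0.5 × 0.201 = 0.10 points.

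These are 5% and 17% of the 0.6 target. At slope 1 the shift is zero.

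**The case against.** The strongest reply is that the article never excludes V1 DAS28. It describes a multivariate model and invites consideration of all other independent measures. A model with only arm and center has no continuous covariate, so calling the similar secondary model an analysis of covariance suggests that a baseline score was intended. A journal article may also leave the covariate list to a fuller document. This stands in part: baseline adjustment is not prespecified, which is different from ruled out. But the article does state a primary model. It fixes center in it and leaves the outcome's own baseline, at most, in an open list. The covariance wording hints at an intention without committing to it.

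Three stronger readings are tempting, and the document does not support them.

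- *The planned analysis is wrong or biased.* It is not. In a randomized trial the change-score comparison is valid and unbiased on average over randomizations. What is lost is precision, plus protection against the particular imbalance that occurs.
- *The gain is large.* Assuming equal variances at both visits and correlations of 0.4 to 0.7 would give larger gains than those above. With a change SD of 0.6, though, this implies a baseline SD of 0.6/√(2(1 − 0.4)) = 0.55 up to 0.6/√(2(1 − 0.7)) = 0.77. The entry range gives 0.55 for a uniform spread, and a larger value would need patients to cluster at its limits.
- *The omission explains why the 75% reference lies below the stated 80%.* It does not. That gap comes from how dropout was allowed for and from using the t rather than the normal distribution. It is a separate matter and adds no weight here.

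**Conclusion.** The point holds as a free improvement and not as an error. The primary model commits to center alone, and whether V1 DAS28 enters is left open. Under the assumed baseline SDs and slopes, the gain from fixing it is between about 1 and 9 percentage points of power at 15 per arm (75% to about 76%–84%). It also removes a shift of about 0.03 to 0.10 points for a one-SD chance imbalance. At slopes near 0.8 the gain is only 1 to 2 points, and at slope 1 it is nil. The slope and baseline SD are assumptions; only the entry range gives them any anchor in the document. The stated sample size of 16 per group is not called into question by this point.

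**What to change.** State the primary analysis as an analysis of covariance of V4 DAS28 (or, equivalently for the treatment effect, of the change) on arm, center and V1 DAS28, with all three terms fixed in advance. For HAQ and GOHAI, specify arm, center and the V1 value of the same score.

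The cost is one degree of freedom per model and a sentence or two of text. DAS28, HAQ and GOHAI are already scheduled at V1 for both groups (Table 1), so no data collection changes. The Trial status section reports nine patients enrolled with the study ongoing, so the change can be recorded before the outcome analysis.

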### V1 - inclusion visit

#### Inclusion criteria

• No change relative to pre-inclusion criteria or exclusion criteria at V0.

• Periodontitis (at least one site with periodontal probing depth ≥ 4 mm and clinical attachment level ≥ 3 mm on at least four different teeth).

• Moderate RA activity according to European League Against Rheumatism (EULAR) criteria, defined as DAS28 of 3.2 to 5.1 [38].

• Provision of informed consent (after 1 week cooling-off period).

• No planned changes in medication, dose or formulation of RA treatment during the following 3 months. No change in disease modifying anti-rheumatic drug treatment will be allowed during the 3 months of the study duration. In cases of painful flare, (defined as an increase of more than 0.6 on the DAS28, or as a pain assessed as greater than 50 on a visual analog scale), use of analgesic (non-steroidal anti-inflammatory drug or at worst, morphine derivatives) or steroidal anti-inflammatory drug (cure in less than 6 days) will be allowed. If these are insufficient, then if the patient’s condition requires it, a treatment change can be established by medical staff. In such cases, patient will not be excluded from the study but it will be taken into account in the statistical analyses (see section on Statistical methods).

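### The two DAS28 worsening outcomes are assigned to logistic regression although the planning values imply fewer than one treated event on each, so a standard odds ratio may often not be finite (low priority)

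*Protocol article*

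**What the plan says.** The Statistical methods section of the protocol article adds five binary versions of the 3-month DAS28 to the primary analysis. Three describe improvement or a low final level. The other two describe worsening: "a relative increase greater than 10% and an absolute increase greater than 0.6) will be evaluated in logistic regression models". The section names no estimator, event rate or covariates for these models, and no rule for an arm without events. An exact method is named only for comparing adverse-event proportions.

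The planning values are in the same section. "Sample size calculation is based on detecting a difference of 0.6 points in DAS28 change from baseline between the two groups". The section continues: "Assuming a standard deviation of 0.6 [28] and using a two-sided test at the 5% significance level". This gives 16 patients per group for 80% power. On enrolment: "Anticipating a 25% dropout rate, the target sample size was thus set at 40 participants". The General design section sets two parallel groups "with a balanced 1:1 treatment allocation", so 20 are enrolled per arm.

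Two other places bear on event rates. The inclusion criteria restrict entry to moderate activity, "defined as DAS28 of 3.2 to 5.1". The Discussion comments on the size of the effect: "We acknowledge that 0.6 mean improvement could be considered as relatively large, but two other trials have shown such an improvement". The mean change expected in the control group is not stated anywhere.

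**The concern.** A treatment that lowers DAS28 makes worsening rare in the treated arm, and the arms are small. If an arm has no events, the likelihood for the treatment log odds ratio keeps rising as the coefficient goes to minus or plus infinity. Software then prints a very large coefficient with a very large standard error, and the Wald interval carries no information. Adjusting for center or weighting complete cases does not help, because neither creates an event in an empty arm.

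If this happens without a named fallback, the analyst has to choose another method after seeing the counts. These are the plan's only binary measures of RA worsening, and the Discussion gives disease stabilization as one expected benefit. A usable estimate is therefore worth having.

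**Working it through.** **Inputs from the protocol article**
- Difference in DAS28 change 0.6, SD 0.6, two-sided 5% (Statistical methods).
- 16 per arm for the power calculation; 40 enrolled, so 20 per arm; 25% dropout leaves 40 × 0.75 = 30, or 15 per arm.
- Baseline DAS28 3.2 to 5.1 (inclusion criteria), so a 10% rise is 0.32 to 0.51 points.

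**Assumptions not in the article**
- Changes are normally distributed.
- Mean change is 0 in controls and −0.6 in treated patients (varied below).
- Baseline is uniform on 3.2 to 5.1.

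**The plan's own figure.** n = 2 × (1.96 + 0.84)² × 0.6² / 0.6² = 15.7, rounded up to 16 per arm. Power at 16 is 80.7% by the normal formula and 78.1% by the noncentral t. The stated 16 is reproduced.

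**Event risks**
- Absolute increase above 0.6: treated P(Z > (0.6 + 0.6)/0.6) = P(Z > 2) = 0.0228; control P(Z > 1) = 0.1587.
- Relative increase above 10%, averaged over baseline: treated 0.0460, control 0.2455. At the mid-range baseline of 4.15 the treated risk is P(Z > (0.415 + 0.6)/0.6) = 0.0454.

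**Probability of no finite odds ratio.** For these two outcomes this is the chance that at least one arm has zero events: a + b − ab, with a = (1 − p_treated)ⁿ and b = (1 − p_control)ⁿ.
- Absolute, n = 16: a = 0.692, b = 0.063, giving 0.711.
- Absolute, n = 20: a = 0.631, b = 0.032, giving 0.643.
- Relative, n = 16: a = 0.470, b = 0.011, giving 0.476.
- Relative, n = 20: a = 0.390, b = 0.004, giving 0.392.

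| Outcome | n per arm | Expected treated events | Expected control events | No finite odds ratio |
|---|---|---|---|---|
| Increase > 0.6 | 15 | 0.34 | 2.38 | 73% |
| Increase > 0.6 | 16 | 0.36 | 2.54 | 71% |
| Increase > 0.6 | 20 | 0.46 | 3.17 | 64% |
| Increase > 10% | 15 | 0.69 | 3.68 | 50% |
| Increase > 10% | 16 | 0.74 | 3.93 | 48% |
| Increase > 10% | 20 | 0.92 | 4.91 | 39% |

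A simulation of 200,000 trials agreed: 71% and 47% at 16 per arm, 64% and 39% at 20.

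**Sensitivity to the control mean change**, same 0.6 difference, 20 to 16 per arm:

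| Control mean change | Increase > 0.6 | Increase > 10% |
|---|---|---|
| −0.3 (controls improve) | 91–94% | 77–82% |
| 0 | 64–71% | 39–48% |
| +0.3 (controls worsen) | 25–33% | 8–14% |

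**Other sensitivities at 16 per arm, control mean 0.** Half the planned effect gives 37% and 14%. An SD of 0.8 gives 34% and 18%; an SD of 1.0 gives 15% and 7%. For the relative outcome, the chance of no treated events is 36% if every baseline is 3.2 and 59% if every baseline is 5.1.

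**The other three outcomes** are much less exposed. At 16 per arm, the chance that an arm has no events or all events is 12% (level below 3.2), 6% (decrease above 0.6) and 1% (decrease above 10%).

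**What a penalized fit gives.** With 0/16 treated against 3/16 control, the maximum-likelihood odds ratio is 0 (log odds ratio minus infinity). Firth's method, which for a single 2 × 2 table adds 0.5 to each cell, gives (0.5 × 13.5)/(16.5 × 3.5) = 0.12.

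**The case against.** The strongest reply is that the article says only that logistic regression will be used. Penalized and exact versions are also logistic regression, and the choice may be made in an analysis plan that is not shown. A reader might infer that the authors chose unpenalized maximum likelihood with Wald intervals; the text does not say so. This stands. What remains is that the method in its default form fits poorly with the counts that the planning values imply.

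Second, the plan fixes a difference between groups, not a control mean. The Discussion's reference to a mean improvement of 0.6 suggests a control mean near 0, but its mention of stabilization also fits controls who worsen, where the problem is smallest. This stands too, so the rates have to be given as a range.

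Third, a reader might infer that no treated events at all are expected on either outcome. For the relative increase this is wrong: 0.74 to 0.92 events are expected, and at least one is more likely than not (53% at 16 per arm, 61% at 20).

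Fourth, it is tempting to say that the events cannot support the planned adjustment. The article states no covariates for these logistic models, so that charge has no basis in the text.

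Finally, these outcomes are supplementary and already subordinate to the continuous analysis. Counts such as 0/16 against 3/16 can be reported whatever the model does. This stands and limits the weight of the point.

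**Conclusion.** The point holds as a low-priority improvement. With a control mean change of 0, both worsening outcomes are expected to have fewer than one treated event. A standard maximum-likelihood odds ratio would then be non-finite in roughly two of three trials for the absolute increase and in two of five to one of two for the relative increase.

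These rates rest on normal changes, the plan's SD of 0.6, a uniform baseline and, above all, the assumed control mean. Across control means from −0.3 to +0.3 they run from 94% down to 25% (absolute) and from 82% down to 8% (relative). Failure is therefore a realistic prospect, not a certainty.

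A reader might conclude that the trial's main result is at risk. It is not: the primary analysis compares continuous DAS28 change and does not depend on these models. Nor do the five outcomes need to be relabelled, since the article already presents them as additional to the primary analysis.

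**What to change.** State in advance how the binary DAS28 outcomes will be estimated. Suggested wording: *The binary DAS28 outcomes will be analyzed by Firth-penalized logistic regression with terms for arm and center only, with profile-likelihood confidence intervals. The number of events and of patients will be reported by arm for each outcome.* A center-stratified exact analysis is an acceptable alternative. If the analysis plan already specifies one of these, nothing further is needed.

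The cost is a line of text and a standard R package; R is already the planned software. Firth estimates are slightly shrunk toward no effect, and exact methods are somewhat conservative. Either way, few covariates can enter these models. Sample size, data collection and the primary analysis do not change.
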